## Discussion

The identification of number and size of prostate cancer lesions prior to RARP has been limited to the 2D view of mpMRI scans and biopsy results. Surgeons are expected to mentally construct and visualise the exact location and dimensions of the lesions in 3D format prior to surgery [10]. The aim of prostate cancer surgery is to preserve maximum nerve function whilst preventing PSMs in order to achieve good functional outcomes. To accomplish this, a better understanding of prostate cancer lesions and the surrounding anatomy is needed [14]. 3D modelling has the potential to enhance surgical planning by providing surgeons with an intra‐operative navigation tool to better appreciate the nature of lesions [11].

A few studies have been conducted using either 3D virtual models or 3D printed models for RARP. Despite varying results, a number have shown a decrease in PSM rates irrespective of the model used; however, only one showed a statistically significant improvement [15]. That study, by Checcucci et al. [20], involved a total of 800 patients, with 3D virtual models created for 640 of these patients. The authors showed a PSM rate of 25% in the 3D virtual model group vs 33% in the control group [20]. To date, most studies have not used inclusion criteria that involve type of lesion, location of lesion, tumour stage or Gleason score [10, 11, 20, 21, 22, 23]. Because a lesion location that is close to the capsule or NVBs can make a significant difference to how conservatively the surgeon approaches the NVBs and the likelihood of PSMs, we have decided to exclude anterior lesions and lesions located far from the capsule to assess the true impact of the models. In addition, most studies have looked at either 3D virtual or 3D printed models [15]. In order for us to assess which is more effective in a similar cohort of patients at a single centre, we have chosen to compare both. This will help us further decide which type of model to use for a randomised controlled trial in the future.

Despite evidence showing a reduction of PSMs, comparatively few data are available showing the impact of 3D prostate models on functional outcomes, with a recent meta‐analysis showing no clear difference in postoperative and functional outcomes in the intervention groups [15]. For this reason, we will follow up patients at regular intervals for up to a year to assess the effects on incontinence and potency.

The surgical lead for this proposal has run an Idea, Development, Exploration, Assessment, Long‐term follow‐up (IDEAL) Phase 2a study on the use of patient‐specific 3D printing in RARP in a cohort of 10 patients with intermediate and high risk of prostate cancer (T3 stages). Despite the small sample size, the outcomes of this study were crucial: PSM rates were reduced from ~35% to 10% [14]. In this study, improvement in tactile appreciation of the size, number and location of the lesions via 3D printing may have proved useful.

In all the work mentioned above, manual delineation of organs on medical images is required, a process known as medical image segmentation. Prostate segmentation is typically performed manually on preoperative T2‐weighted MRI to produce a 3D anatomical shape of the prostate gland, whereas prostate cancer lesion segmentation is conducted manually on mpMRI to generate 3D representations of the location of cancer lesions. Both tasks are time‐consuming and require substantial radiological expertise. Moreover, manual segmentation is not scalable and is prone to human error. Therefore, a reliable automated approach for prostate and cancer lesion segmentation is crucial to overcome some of the limitations of translating 3D virtual models and 3D printed models into clinical practice and into the operating theatre.

Our group has recently made substantial progress towards the automated segmentation of the prostate gland and cancer lesions, developing technologies that are timely and innovative for this proposal. In particular, our group has designed MONAI Labels, a labelling and learning tool that helps researchers and clinicians rapidly build artificial intelligence models to create segmentation datasets, for use in a study currently under review [24].

## Participant Discontinuation and Withdrawal Criteria

Patients can choose to completely withdraw from the study before surgery. Once patients sign the written consent form prior to surgery, data will be collected. However, one foreseeable circumstance is a patient dying before or just after surgery, which will make data collection impossible. If a patient decides to drop out of the study after providing consent, they will be withdrawn from our study, but their data will still be used to report metrics related to the implementation of our study.

Patients who withdraw from the study will be replaced by other patients following covariate assignment to avoid bias within a cohort and to guarantee that all cohorts have the required number of patients.

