### Endpoints

The primary study outcome is PSM rates measured after specimen analysis. Secondary outcomes include incontinence rates (pad weights, electronic Patient‐Reported Outcome Measures), erectile dysfunction (International Index of Erectile Function score, and Erectile Hardness Score), and International Consultation on Incontinence Questionnaire‐Urinary Incontinence (ICIQ‐UI) score captured at 3 months after surgery. Other secondary outcomes are related to our pipeline deployment metrics, including patient recruitment rate and percentage of cases that led to successful model deployment in the theatre.

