## Methods

### Interventions

Patients diagnosed with prostate cancer will undergo discussion at the weekly multidisciplinary team meeting at Guy's Hospital (London, UK) to decide management options. These patients will then be followed up in the clinic to determine those who opted for RARP. A list of those scheduled for RARP in the upcoming months will be collected. Patients will fill out questionnaires in the clinic regarding baseline functional information preoperatively related to potency and continence and these data will be stored on REDCap (Research Electronic Data Capture software). The hospital electronic health record will be used to collect data on patient demographics, staging, Gleason score, prior treatment for prostate cancer, potency and incontinence to eliminate patients not meeting our inclusion criteria.

Patients will then be contacted via telephone and informed about the study. They will be given written information via e‐mail or in person preoperatively on: (i) the aims of the study; (ii) the patient information materials available; and (iii) contact details of chief investigator.

Patients can consent verbally to participate in the study via telephone but can opt to withdraw any time before the surgery. They will then be given a written consent form to sign before their surgery, which will include permission to use their data. Pseudo‐anonymisation will be carried out by a Clinical Research Fellow to allow data processing and analysis by Data Scientists.

Once patients have consented verbally, mpMRI will be obtained and anonymised for extraction of anatomical structures. Histology data will also be collected from previous prostate biopsy to help better identify the exact location and size of lesions. These will then be reviewed by the radiologist to guarantee the patient is eligible given our inclusion criteria.

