### Methods of Data Collection

This will be a single‐centre study performed in the Urology Department of Guy's Hospital, London, UK. Specimen analysis will be carried out on the whole prostate gland removed from the patient during RARP to evaluate margin status and estimate PSMs. There will be no deviation from normal clinical practice.

At the 6‐week follow‐up, the surgeon will meet with the patient to present PSM status and capture functional outcomes from the patient via questionnaires. We will capture these measures as endpoints for analysis. These questionnaires will be re‐administered at 3, 6 and 12 months postoperatively.

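### The withdrawal and replacement rule is not limited to the period before surgery, so it could drop margin results already known and select on the primary outcome

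*Protocol article*

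**What the plan says.** The section Participant Discontinuation and Withdrawal Criteria deals with three things.

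- **Withdrawal before surgery.** "Patients can choose to completely withdraw from the study before surgery". The Interventions section gives the same window: men who consent by telephone "can opt to withdraw any time before the surgery".
- **Drop-out after consent.** "If a patient decides to drop out of the study after providing consent", the consequence is that "they will be withdrawn from our study, but their data will still be used to report metrics related to the implementation of our study". No end point is given for this period. Written consent is signed before surgery.
- **Replacement.** "Patients who withdraw from the study will be replaced by other patients following covariate assignment to avoid bias within a cohort", and also "to guarantee that all cohorts have the required number of patients". No time limit is given here either.

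The timing of the primary outcome is set elsewhere. Under Endpoints, "The primary study outcome is PSM rates measured after specimen analysis". Under Methods of Data Collection, the surgeon meets the patient at 6 weeks to "present PSM status and capture functional outcomes from the patient via questionnaires", and the questionnaires are repeated at 3, 6 and 12 months. The same section says that specimen analysis follows normal clinical practice.

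**The concern.** Once the specimen has been examined, PSM status needs nothing further from the patient, so it should be close to complete in every operated man. The questionnaires are different, because they depend on continued participation for a year.

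The withdrawal rule does not separate the two. Read without a time limit, it lets a man who stops answering questionnaires at, say, 6 months be withdrawn and replaced, even though his margin result is already on file and he has been told it. If men who leave after the 6-week visit are more often margin-positive, the analysed PSM rate falls below the true rate. The replacement is a new patient whose margin is still unknown. Resemblance on baseline covariates does not restore the lost result, so the stated aim of avoiding bias is not met for these men. Filling each cohort to its planned number would also make the loss hard to see unless withdrawals and replacements are reported.

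**Working it through.** **Inputs from the protocol article**

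- Control PSM rate: about 20% (Sample Size Determination).
- Group sizes: 54 printed, 54 virtual, 108 prospective control, 54 retrospective control; 54 + 54 + 108 + 54 = 270 (same section).
- Primary test: Pearson chi-squared across three groups at 0.05 (Data Analysis).
- Drop-out rate: none stated. All drop-out values below are assumptions.

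The plan gives no figure for this bias, so there is none to reproduce. The starting point is the expected count in one intervention arm: 54 × 0.20 = 10.8 margin-positive men.

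**Step 1. Analysed rate when men leave after surgery and are replaced**

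Let p be the true PSM rate, a the drop-out among margin-positive men and b the drop-out among margin-negative men. If replacements are subject to the same drop-out, then

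analysed rate = p(1 − a) / [p(1 − a) + (1 − p)(1 − b)]

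With p = 0.20:

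| a | b | Calculation | Analysed rate | Shift (points) |
|---|---|---|---|---|
| 5% | 5% | 0.19 / (0.19 + 0.76) | 20.0% | 0 |
| 10% | 3% | 0.18 / (0.18 + 0.776) | 18.8% | −1.2 |
| 20% | 5% | 0.16 / (0.16 + 0.76) | 17.4% | −2.6 |
| 30% | 5% | 0.14 / (0.14 + 0.76) | 15.6% | −4.4 |

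The first row shows that equal drop-out produces no bias. Drop-out before surgery also produces none of this kind, because no margin result exists to select on.

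**Step 2. The same effect in patients**

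If m margin-positive men in an arm of 54 are replaced by men with an expected rate of 20%, the expected count is 10.8 − m + 0.2m = 10.8 − 0.8m.

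- m = 1: 10.0 / 54 = 18.5%
- m = 2: 9.2 / 54 = 17.0%
- m = 3: 8.4 / 54 = 15.6%

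For scale, the standard error of a 20% rate in 54 men is √(0.20 × 0.80 / 54) = 5.4 points.

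**Step 3. Effect on the primary test in an unfavourable case**

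Suppose there is no true difference, only margin-positive men leave, and they leave in the two intervention arms only. The three-group chi-squared test was simulated at 54/54/108 with 200,000 runs.

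| Drop-out of margin-positive men | Analysed rate, intervention arms | Rejection rate |
|---|---|---|
| 0% | 20.0% | 5.0% |
| 10% | 18.4% | 5.4% |
| 20% | 16.7% | 7.4% |
| 30% | 14.9% | 11.6% |
| 50% | 11.1% | 32.3% |

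The inflation is slight at 10% and matters only when a substantial share of margin-positive men leave, and only in the intervention arms.

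**Step 4. With every operated man retained**

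The expected rate stays at 20% (10.8 of 54) whatever the later drop-out, and no replacement is needed after surgery.

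**The case against.** The strongest answer is that the authors probably meant withdrawal before surgery. Both places that give a withdrawal window tie it to surgery, and the replacement sentence uses the same verb. Men who leave before surgery have no margin result, so replacing them cannot select on it. This stands as a plausible reading of intent. It does not settle the matter, because the drop-out sentence starts at consent and has no end, the replacement sentence has no limit, and the section itself looks past surgery when it mentions death shortly afterwards.

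Several stronger readings are tempting, but the documents do not support them.

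- A reader might infer that every man who leaves at any time up to 12 months is stated to lose his PSM result. The text does not say this. It names one use of his data without excluding others, and it does not mention the 12-month point. Equally, nothing says that a result already obtained is kept.
- A reader might see a contradiction with the allocation of men to the printed or virtual model by time and resources (Surface Model Generation). That section describes initial allocation. Choosing a comparable replacement need not conflict with it.
- A reader might argue that unblinded surgeons make drop-out differ by arm. The text makes drop-out the patient's decision and says that the analysis is blinded. Differential drop-out by arm is possible but is an assumption.

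It is also fair to say that the shifts in Step 1 are smaller than one standard error of a single arm, and that this is a non-randomised feasibility study with other sources of bias. Detailed analysis populations may be left to documents not shown. The point here concerns a rule that the article does state, together with the claim that it avoids bias.

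**Conclusion.** The concern holds as a badly bounded rule. It is not a demonstrated exclusion of outcomes. As written, the article permits replacement of men whose primary outcome is already known, and for those men replacement by covariates does not avoid bias.

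With a true PSM rate of 20%, the three assumed drop-out patterns lower the analysed rate by 1.2 to 4.4 points. If the pattern arose in one group only, that amount would appear as a false difference; if it were the same in all groups, the rates would be too low but no false difference would be expected when the true rates are equal. The size rests entirely on assumed drop-out, since the documents give none. It is zero if drop-out is unrelated to margin status or happens before surgery. The change should be made because the potential bias falls on the primary outcome and is easily avoided.

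**What to change.** Amend Participant Discontinuation and Withdrawal Criteria to say that:

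1. only patients who withdraw before surgery are replaced;
2. every consented patient who undergoes RARP stays in his assigned group, and his PSM result enters the primary analysis unless he withdraws permission for data use;
3. drop-out after surgery affects only the questionnaire data not yet collected;
4. withdrawals and replacements are reported by group, with their timing relative to surgery and to the 6-week visit.

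The cost is mainly wording. The sample size does not change, margin status comes from routine specimen analysis, and the Interventions section says that the written consent includes permission to use data. The one item to check is whether that permission covers use after withdrawal. The consent form is not shown; if it does not extend that far, more than a wording change may be needed.

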## Ethical Considerations

The study will be conducted in compliance with the Declaration of Helsinki, Good Clinical Practice, and national laws and guidelines. The protocol was approved by the London Surrey Research Ethics Committee (REC) NHS Health Research Authority (HRA) and Health and Care Research Wales on 29 June 2023 (REC reference: 23/LO/0492 and IRAS project ID: 312298).

Due to the non‐invasive nature of this study, there is minimal risk involved in using these models for RARP. There is a risk of inaccurately displaying lesions on 3D models, which might affect resection. However, this is highly unlikely since 3D models will be constructed from medical images of the patient. To mitigate this risk, radiologists will confirm the identification of prostate anatomical structures and that cancer lesions accurately represent those on medical images, while surgeons will always use the models in the context of the source MRI.

## Data Protection

Patient privacy is one of the main issues when collecting and sharing data. In this feasibility study we will pseudo‐anonymise patient data to respect patient privacy. Methods for database locking at the start of the analysis and storage upon completion of the clinical investigation will be implemented. Data records will be set to read‐only on completion of data collection for analysis.

## Data Availability

Three‐dimensional printed models will be collected by the Clinical Research Fellow after being used during surgery and then returned to the chief investigator. Models will be disposed of in accordance with hospital disposal policies. There will be no identifying information on the models. The laptop running Innersight Labs 3D visualisation will be returned to the chief investigator after study completion. Data collected will be available on request from corresponding authors.
